Therefore, most rheumatologists rather use 7.5 to 10 mg PRED in the initial treatment of RA, increasing the dose in case of lack of efficacy, and tapering the dose over the following weeks to bridge the interval until DMARD become clinically efficacious. Unfortunately, there is insufficient data concerning this dosage schedule.

In order to shed further light on the best possible GC treatment strategy in early RA regarding both efficacy and safety, we have designed a study which may guide future treatment decisions.

The main aims of this study are: to compare the use of GC as a bridging therapy with placebo in a treat-to-target setting with DMARD, and to define the best out of two standard GC dosage regimens. Both aims are with regard to the progression of radiographic joint damage after one year compared to baseline.

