### Sample size

It is assumed that progression of radiographic joint damage as measured by the SHS will be the same for both dosage levels of PRED. For sample size calculation we used data from the BeSt-study [9]. We thus assume an effect of 3.7 and a standard deviation of 7.5. Accounting for a 5% dropout rate, the effect will be 3.5. If 150 patients per group are included, a two sided t-test of superiority (α = 0.05) between one of the PRED groups and the placebo group will give a power of >0.95. Accepting a non-inferiority margin of 1.3 (one third of the known placebo-verum difference) for the difference in progression between the PRED groups, the one sided non-inferiority test in step three (at α = 0.025) will give a power of >0.80, if 149 patients per PRED group are included. The significance level of α = 0.025 was chosen according to the European Medicines Agency guidelines [25]. Thus, the final sample size has been set as 150 patients per group.

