### Blinding and statistical methods

All participating rheumatologists and radiologists will be blinded against the interventions, thus assuring blinded assessment of outcome variables.

The primary endpoint is the progression of radiographic damage after one year compared to baseline (measured by the SHS). Analysis will be performed in three steps to compare the three groups (Pl: placebo group; V10: group starting with 10 mg PRED; and V60: group starting with 60 mg PRED). Primary analysis will be conducted by analysis of covariance (ANCOVA) for V60 versus Pl, using baseline values as covariates and 12-month values as dependent variables. In case of a statistically significant result (α = 0.05), a comparison of V10 versus Pl will be performed (α = 0.05). In case of superiority of V10 versus Pl, a non-inferiority test for V10 versus V60 will be performed (α = 0.025), as is shown in Figure 2. A non-inferiority margin of 1.3 SHS points has been selected.

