## Discussion

The most frequently used dosage of 7.5 to 10 mg PRED as a bridging treatment in early RA is a compromise between the good clinical short-term effect of GC and the attempt to minimize the risk of AE. However, the first months of RA are considered to be like a window of opportunity, with the best offer to change the course of the disease. This window of opportunity should be used to ‘hit hard and early’ (provide aggressive treatment as soon as possible) [14]. It may well be that higher dosages of GC, as used in the COBRA study [8] and the BeSt-study [9], have a higher impact on the outcome without a considerable increase of AE. The answer to this question would be highly relevant for the individual patient because of the increased possibility to induce a more favorable course of the disease. The immediate benefits for society in general and for the economic expenditures in particular are obvious.

The aim of our study is to test different treatment strategies rather than to evaluate the dose-dependent effect of PRED on the Sharp score. This means to find answers to two questions. Firstly, is it worthwhile to start with a high-dose PRED treatment in active RA patients, even if a treat-to-target approach is followed? Secondly, is there any difference between initially high and low PRED doses in the sense of benefit in radiographic progression? In the further course, there are many potential confounders, such as imbalanced MTX use, imbalanced GC use during weeks 13 to 52, and imbalanced use of biologics. These imbalances may flaw the immediate effect of the PRED bridging on the Sharp score, but have only a minor impact on the tested treatment strategies. The possible results of our testing procedure may clarify if high-dose PRED bridging is not superior to a placebo, then the disease modifying effect of PRED no longer plays a major role in a treat-to-target setting. If there is a significant difference between high-dose PRED bridging and placebo, and low-dose PRED bridging is not superior to a placebo, then high-dose bridging may be strongly recommendable. If a low-dose bridging compares to a significantly effective high-dose bridging, the EULAR recommendation of merely regarding the symptomatic effect of PRED is confirmed. If there are no differences between all three groups even with sufficiently imbalanced concomitant therapies, then only symptomatic effects of PRED should guide treatment decisions.

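### The Discussion's pre-stated readings of the test sequence can mislead on dose, or on lack of effect, if the true effect is smaller than planned

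*Protocol article*

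**What the plan says.** The section on blinding and statistical methods sets a fixed order for one-year SHS progression: V60 against placebo, then V10 against placebo, and last the only direct dose comparison, which is conditional: "In case of superiority of V10 versus Pl, a non-inferiority test for V10 versus V60 will be performed".

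The Discussion attaches conclusions to the outcomes of this sequence:

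- Step one fails, under treat-to-target care: "if high-dose PRED bridging is not superior to a placebo, then the disease modifying effect of PRED no longer plays a major role".
- Step one succeeds and step two fails, so that V60 alone is significant: "and low-dose PRED bridging is not superior to a placebo, then high-dose bridging may be strongly recommendable".
- No differences among the three groups: only symptomatic effects should guide treatment.

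The Background gives as a main aim "to define the best out of two standard GC dosage regimens", judged by radiographic progression. The Discussion likewise poses, as its second question, whether the high and low starting doses differ in radiographic benefit.

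The sample size section supplies the planning values: "We thus assume an effect of 3.7 and a standard deviation of 7.5". The planning effect is then lowered for missing patients: "Accounting for a 5% dropout rate, the effect will be 3.5". The group size follows at the end of the section: "Thus, the final sample size has been set as 150 patients per group". It also assumes equal progression under both prednisolone doses.

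**The concern.** There are two inference problems.

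First, one significant and one non-significant result against the same placebo arm do not show that the two active arms differ. The Discussion moves from that pattern to a possible strong recommendation for one regimen, in the very branch where the sequence rules out a test of V10 against V60. The comparison of regimens is a stated aim, so this is where a reader would look for the answer.

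Second, failure to show superiority is not evidence that an effect is too small to matter. No interval or equivalence criterion is attached to the statement of no major role, and the word major is not defined. The reading of no differences among all three groups has the same weakness: once step one has failed, nothing further is tested, so it could rest only on non-significance or description.

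At stake is a published statement about dose choice, or about the value of bridging, that the data need not support.

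**Working it through.** **Inputs.** From the sample size section: effect 3.5 after dropout (3.7 before), SD 7.5, 150 per arm, two-sided α = 0.05, equal effect of both doses. From the statistical methods: the test order and the 1.3-point non-inferiority margin. Assumptions made here: normal arm means, known SD, and no gain in precision from baseline adjustment. The true effects below 3.5 are assumed values, shown as a range.

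**The plan's own figure.** The sample size section states that "a two sided t-test of superiority (α = 0.05) between one of the PRED groups and the placebo group will give a power of >0.95".

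- SE of a difference = 7.5 × √(2/150) = 0.866.
- Power at 3.5 = Φ(3.5/0.866 − 1.96) = Φ(2.08) = 0.98. The stated figure reproduces.

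**How often V60 alone is significant when the doses are equal.** Let z60 and z10 be the two test statistics against placebo. Each has mean δ/0.866 and variance 1. Their correlation is 0.5 because they share the placebo arm. Then

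P(V60 only) = P(z60 > 1.96) − P(z60 > 1.96 and z10 > 1.96).

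The V60-V10 difference counts as favouring V60 if its own z exceeds 1.96. Exact bivariate-normal values agree with 2,000,000 simulated trials:

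| True effect δ, both doses | Step one fails | V60 only | V60 only, share of trials passing step one | Direct comparison favours V60, share of V60-only trials |
|---|---|---|---|---|
| 3.5 | 1.9% | 1.6% | 2% | 24% |
| 3.0 | 6.6% | 4.8% | 5% | 18% |
| 2.5 | 17.7% | 10.4% | 13% | 14% |
| 2.0 | 36.3% | 15.6% | 24% | 12% |
| 1.75 | 47.6% | 16.6% | 32% | 12% |
| 1.3 | 67.7% | 14.8% | 46% | 13% |
| 1.0 | 79.0% | 11.7% | 56% | 14% |

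Example, δ = 2.0: P(z60 > 1.96) = Φ(2.309 − 1.96) = 0.637; both significant 0.481; difference 0.156; share 0.156/0.637 = 0.24.

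**Dependence on the SD.** With margin 1.3, one-sided α 0.025 and power 0.80, the stated 149 per prednisolone group implies an SD of 1.3/[(1.96 + 0.842) × √(2/149)] = 4.0, not 7.5. That mismatch is a separate matter. With SD 4.0 the V60-only pattern falls to 0.8% at δ = 2.0 and about 0% at 3.5, but is still 16% at δ = 1.0.

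**What a failed step one excludes.**

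- 95% CI half-width = 1.96 × 0.866 = 1.70.
- Non-significance means an observed benefit below 1.70, so the upper limit is below 1.70 + 1.70 = 3.40. An observed 1.6 gives an upper limit of 3.3.
- The planned 3.5 and 3.7 are therefore excluded. A benefit of 2 or 2.5 need not be.
- The exclusion of 3.5 is narrow: it needs an observed SD below 3.5/[2 × 1.96 × √(2/150)] = 7.7.

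**Would 1.3 serve as the bound for no major role?** The upper limit falls below 1.3 only if the observed benefit is below 1.3 − 1.70 = −0.40. If V60 truly has no effect, this happens with probability Φ(−0.40/0.866) = 0.32. A truly null result would be called inconclusive about 68% of the time.

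**The case against.** Several points on the other side are good.

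- **Frequency.** A reader might infer that wrong dose conclusions are likely. The documents do not support that. Under the protocol's own inputs the V60-only pattern occurs in about 1.6% of trials and step one fails in 1.9%. The problem becomes material only at effects well below plan.
- **Binding force.** A reader might also infer that the plan commits the investigators to firm conclusions. The sentences stand in the Discussion, not in the methods, and are hedged by words such as may and major. The text that follows asks for other endpoints to be weighed and allows that uncertainty could remain and a confirmatory trial be needed.
- **Meaning of major.** If it means an effect of the planned size, a failed step one does exclude that, as shown above.
- **Literal wording.** In the second branch V60 is the only regimen shown superior to placebo, and the text does not literally say that it beats V10.
- **Reporting.** A hierarchy limits confirmatory claims and does not forbid estimates. Nothing says that the intervals will be withheld, and their listing may be left to a fuller document.

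These points limit the size of the concern but do not remove it. The allowance for uncertainty gives no rule for when a result is inconclusive, and the same paragraph insists that the primary endpoint not be blurred by short-term results. Calling high dose possibly strongly recommendable because low dose missed significance invites a comparison that the sequence never makes.

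A smaller effect is also not far-fetched on the protocol's own text. The planning effect comes from a trial that the Background groups with 60 mg regimens tapered over six to eight months, while the intervention here lasts 12 weeks with treat-to-target escalation in every arm. This is a reason to make the readings robust. It does not predict that the effect will be small.

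**Conclusion.** The point holds as a conditional one: the pre-stated readings can mislead if the true effect is smaller than planned.

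1. **Dose.** With equally effective doses, a V60-only result arises in about 15 to 17% of trials at true effects of 1.3 to 2.0, which is 24 to 46% of trials that pass step one. A direct comparison would support V60 in only about one in eight of these. At the planned effect the figure is about 1.6%.
2. **No major role.** A failed step one rules out the planned effect, narrowly, but leaves benefits of up to about 3.4 points open. At a true benefit of 2.0 it would occur in 36% of trials.

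The figures rest on SD 7.5, 150 per arm and no precision gain from baseline adjustment; a smaller SD moves the vulnerable range to smaller effects. The finding concerns inference only and takes no view on either dose.

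**What to change.** - Report the adjusted V60-placebo, V10-placebo and V60-V10 differences with 95% confidence intervals wherever the hierarchy stops, labelled as estimates outside the confirmatory sequence where no test is reached. The testing order and α are unchanged.
- Reword the Discussion so that any statement that one regimen is better than the other on SHS rests on the V60-V10 interval, not on one test succeeding and the other failing.
- State no major role, or no differences, only if the interval excludes a pre-specified benefit over placebo that the investigators justify for that purpose. The 1.3-point margin should not be borrowed: it was set for the comparison between the prednisolone groups, and a truly null V60 would meet it in only about 32% of trials.
- In all other cases call the result inconclusive.

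The cost is a rewording of the interpretation and analysis paragraphs, the work of justifying one bound, and the acceptance that some results will be inconclusive. No change to design, sample size or treatment is needed.

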## Trial status

Recruitment started in February 2014 and is expected to finish in 2016.

## Abbreviations

AE: Adverse events
CI: Confidence interval
DAS28: Disease Activity Score 28
DMARD: Disease-modifying antirheumatic drug
DRKS: German Clinical Trials Register
DSMB: Data and safety monitoring board
DXA: Dual-Energy X-ray Absorptiometry
ESR: Erythrocyte sedimentation rate
EudraCT: European Union Drug Regulating Authorities
EULAR: European League Against Rheumatism
FFbH: Physical functioning questionnaire Hannover
GC: glucocorticoid
ITT: Intention-to-treat
MTX: methotrexate
Pl: Placebo group
PRED: prednisolone
RA: Rheumatoid arthritis
sd: Standard deviation
SHS: van der Heijde modification of the Sharp score
V10: Group starting with 10 mg prednisolone
V60: Group starting with 60 mg prednisolone.
